### **Study Duration**

Participants were asked to receive the intervention throughout their hospitalization and during post-discharge home rehabilitation and were followed for 3 months.

### **Study Population**

This emulated target trial was conducted at the First Affiliated Hospital of Bengbu Medical University, including 164 UA patients who underwent PCI in the Department of Cardiology from April to May 2022 (the control group) and May to June 2022 (the intervention group). Main inclusion criteria were as follows: (1) Patients diagnosed with UA who successfully underwent PCI; (2) patients classified as having cardiac function grades 1 to 3; (3) patients with no new or recurrent chest pain for at least eight hours after reperfusion therapy, no new arrhythmias or ECG changes within this timeframe, and no further elevation in myocardial injury marker levels; (4) patients capable of using a smartphone; and (5) patients who understood the purpose of this study and voluntarily provided written informed consent. The exclusion criteria were as follows: (1) patients with significant postoperative wound bleeding, severe infection, fever, severe electrolyte–acid–base imbalance, severe

hypoxia, or malnutrition; and (2) patients who were unwilling to participate in this study or unable to adhere to the follow-up visit requirements.

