159 research team will ensure that patients have signed the informed consent form before  
160 entering the study and will provide ongoing support and guidance throughout the  
161 study.

162 After the recruitment and pre-screening processes, patients were divided into two  
163 groups based on their admission dates: the control group (April to May 2022) and the  
164 intervention group (May to June 2022). In addition to receiving standardized  
165 treatment, the intervention group also received a multidimensional digital cardiac  
166 rehabilitation intervention, which encompassed seven dimensions: exercise training,  
167 medication management, nutritional guidance, psychological support, sleep  
168 management, health education, and smoking cessation support. It is important to note  
169 that, in addition to the intervention for patients themselves, the digital cardiac  
170 rehabilitation intervention particularly emphasized the involvement of the patients'  
171 family members. During the hospitalization period, family members were invited to  
172 participate in the rehabilitation training program, ensuring that they could provide

necessary support for the patients and promote health education within the home environment. The control group, on the other hand, received only standardized treatment and standard nursing care.

After the PCI procedure, both groups of patients underwent a three-month follow-up period. The follow-up included individualized educational sessions conducted monthly via the WeChat platform, in addition to outpatient visits at one and three months post-surgery. During the follow-up, patients were required to report their health status to the multidisciplinary intervention team, including blood pressure, physical activity, dietary habits, sleep patterns, psychological state, and progress in smoking cessation.

Only patients who completed all data collection requirements were included in the final analysis. The final dataset was subjected to propensity score matching to balance the baseline characteristics between the two groups, ensuring comparability.

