### **Randomization**

Owing to the nature of the intervention, the participants were not randomly assigned. To minimize potential confounding factors, the multidimensional digital cardiac rehabilitation intervention group and the usual care group were matched on the basis of propensity scores calculated using logistic multiple regression analysis. The matching process involved considering covariates such as age, sex, education level, marital status, exercise habits, monthly salary, current address, living arrangement

(solitary or not), history of CHD, history of PCI, length of hospitalization, medical insurance status and polypharmacy data obtained from presurveys. Propensity score analysis was conducted using a 1-to-1 ratio matching approach with the nearest neighbour method to ensure balanced characteristics between the intervention and control groups. A standard calliper width of 0.2 was used for the propensity score. After matching, a total of 136 patients were included, with 68 patients in the multidimensional digital cardiac rehabilitation group and 68 patients in the usual care group.

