## Discussion

Findings indicated that a multidimensional digital CR intervention improved functional status (FP, 6MWT, gait speed, and 30-s CST) and metabolic markers (TC, TG, and LDL-C) in patients with UA undergoing PCI within a relatively short period compared to standard management. These results emphasize the program's potential to enhance physical recovery and cardiovascular health. Significant time effects were also observed for grip strength, WC, BMI, and overall quality of life (physical and mental components), reinforcing the efficacy of digital interventions. This novel rehabilitation model provides CVD education, clarifies essential diagnostic procedures, provides exercise rehabilitation guidance, and supports home-based rehabilitation. Promoting physical activity, encouraging lifestyle modifications, and facilitating behavioral changes during recovery contribute to improved quality of life in patients with UA undergoing PCI.

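### Treatment group is set by admission date, so calendar period is confounded with treatment (completely if the May changeover was sharp), and matching on patient characteristics cannot support the causal wording

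*Combined protocol and SAP*

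**What the plan says.** The document calls the study a prospective emulated target trial at one hospital. Study Design says that patients were put into "groups based on their admission dates: the control group (April to May 2022) and the" intervention group (May to June 2022). Study Population gives the same windows: "from April to May 2022 (the control group) and May to June 2022 (the intervention group". Neither section gives the day in May on which recruitment switched.

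The Randomization section states: "Owing to the nature of the intervention, the participants were not randomly assigned". Its answer to confounding is matching: "To minimize potential confounding factors, the multidimensional digital cardiac rehabilitation intervention group and the usual care group were matched" on a propensity score. The covariates are "age, sex, education level, marital status, exercise habits, monthly salary, current address, living arrangement", then "history of CHD, history of PCI, length of hospitalization, medical insurance status and polypharmacy data obtained from presurveys". None of them is admission date, season or ward practice.

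Study Design describes the result of matching this way: "The final dataset was subjected to propensity score matching to balance the baseline characteristics between the two groups, ensuring comparability". The Statistical Method then compares groups by t test, Wilcoxon, chi-square or Fisher's exact test, with no term for calendar time. The Discussion opens: "Findings indicated that a multidimensional digital CR intervention improved functional status", and goes on to metabolic markers, in comparison with standard management.

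**The concern.** Three-month outcomes fall in about July to August for controls and August to September for the intervention group. Anything that changed over those months besides the programme enters the group difference: season, staffing, routine care, or the testers' experience with timed walking and chair-stand tests. Matching can balance only what is in the score. Admission date is the assignment rule itself, so with a sharp changeover, adding it to the score would leave no patients with comparable values in both groups. Good balance on the listed covariates says nothing about period.

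At stake is the between-group conclusion in the Discussion, which covers the frailty phenotype, 6MWT, gait speed, 30-s chair stand, TC, TG and LDL-C. The design cannot separate programme from period for these, no analysis examines the question, and the Discussion does not mention it.

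**Working it through.** **Inputs from the document.** 89 intervention and 75 usual-care patients before matching (89 + 75 = 164); 68 per group after matching (68 + 68 = 136); threshold P<0.05, taken as two-sided; admission windows as quoted. The document gives no power calculation, SD or assumed effect, so there is no design figure to reproduce. The stated counts agree with each other.

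**Assumptions.** Windows run from 1 April to 30 June 2022 with even accrual. The drift per month is hypothetical and is shown as a range.

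**1. Calendar gap between groups.**
- Sharp changeover on day c: the mean dates are (1 April + c)/2 and (c + 30 June)/2. The difference is (30 June − 1 April)/2 = 90/2 = 45 days, wherever in May c falls.
- Both groups recruiting throughout May: the mean dates are about 1 May and 31 May, a gap of about 30 days.

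The gap is therefore 1 to 1.5 months, and the three-month visits shift by the same amount.

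**2. What a drift would do.** The standard error of a difference in means is √(2/68) = 0.171 SD. The false difference is drift × gap. With no true effect, the chance of P<0.05 is P(Z > 1.96 − shift/SE) + P(Z < −1.96 − shift/SE).

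| Assumed drift per month | False difference | Chance of P<0.05 |
|---|---|---|
| 0 | 0 | 5% |
| 0.05 SD | 0.05-0.08 SD | 6-7% |
| 0.1 SD | 0.10-0.15 SD | 9-14% |
| 0.2 SD | 0.20-0.30 SD | 22-42% |

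An observed difference of 1.96 × 0.171 = 0.34 SD reaches P<0.05.

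**3. What adjusting for admission date costs.** Let r be the correlation of group with date. The standard error is multiplied by √(1/(1 − r²)).
- Sharp changeover, two windows of 1.5 months: between-group variance of date (1.5/2)² = 0.5625; within-group 1.5²/12 = 0.1875; r² = 0.5625/0.75 = 0.75, r = 0.87. The multiplier is √4 = 2.
- Shared May, two windows of 2 months: between 0.25; within 4/12 = 0.333; r² = 0.25/0.583 = 0.43. The multiplier is √1.75 = 1.32.

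The 95% half-width rises from 0.34 SD to about 0.67 SD (sharp) or 0.44 SD (shared May).

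**4. Whether agreement of the two estimates could be required.** With a sharp changeover the standard errors are 0.171 and 0.342 SD. With no drift at all, the two estimates differ by chance with SD √(0.342² − 0.171²) = 0.30 SD. They would be more than 0.3 SD apart about 31% of the time. A rule that claims an effect only when they agree in size would discard valid effects.

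**The case against.** The lack of randomisation is declared openly, and sequential allocation cannot now be undone. The windows are adjacent, in one department, only 30 to 45 days apart on average, which limits the room for drift. The document contains no seasonal or drift data. The top row of the range needs 0.2 SD per month, or 1.2 SD if sustained for six months, and nothing in the document makes that plausible. Drift could also run against the programme and hide a benefit. All of this stands, and it restricts what can be claimed.

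A reader might infer four stronger things that the document does not support:

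- **That period and treatment are certainly fully confounded.** Allocation by admission date suggests a sharp cut, but both windows name May and no date is given. With a shared May the confounding is strong but partial.
- **That the reported improvement is a calendar artefact, or that the error rate really is 22-42%.** The drift is assumed. The design fails to exclude a period effect; it does not show one.
- **That every outcome is affected equally.** For grip strength, waist circumference, BMI and quality of life, the Discussion cites only time effects, not a difference from standard management.
- **That modelling admission date would settle the matter.** A linear date term leaves a step change in ward practice at the changeover wholly inside the group effect. A trend among intervention patients is also ambiguous, because Development and Quality Control says that the programme was assessed and optimised throughout the study.

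**Conclusion.** The concern holds in a bounded form. Group is determined by admission date, and neither the matching nor the analysis addresses calendar period. Confounding is complete with a sharp May changeover and strong otherwise. The comparability statement in Study Design, and the improvement statement in the Discussion for the seven outcomes compared with standard management, claim more than the design can support.

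The size and direction of any period effect are unknown from the document. The 6-7% to 42% range shows only what an assumed drift of 0.05 to 0.2 SD per month would do, given even accrual, a gap of 1 to 1.5 months and 68 per group. This should be corrected: it changes what the study can conclude, and the correction is cheap.

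**What to change.** **Wording**
- In Study Design and Study Population, state the changeover date and whether both groups recruited at any time during May.
- In Study Design, say that matching balances only the covariates listed under Randomization.
- In the Discussion, replace the causal verb with *was associated with*. Name calendar period, including any step change in ward practice, as an unmatched confounder that these data cannot separate from treatment.

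**Analyses.** Findings are already reported, so these must be labelled post hoc and supportive only.
- (a) Trends by admission date in the recorded admission values for both groups (the document gives admission measurements for physical fitness and lipids), and in three-month outcomes among controls only. The programme cannot explain a trend in either.
- (b) The group difference adjusted for continuous admission date, reported with its confidence interval beside the matched estimate and not used as a condition for claiming an effect.

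**Cost.** A few sentences and a few models on admission dates that the team must hold, since they defined the groups. Under even accrual, the standard error in (b) is about 2 times larger with a sharp changeover and about 1.3 times larger if May was shared, so the interval will be wide. A step change at the changeover remains undetectable whatever is done, which is why the wording matters more than the extra models.

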***Inclusion and exclusion criteria.***

---

Inclusion criteria

---

Age between 18 and 74 years old

Patients diagnosed with UA who successfully underwent PCI

Patients classified as having cardiac function grades 1 to 3

Patients with no new or recurrent chest pain for at least eight hours after reperfusion therapy, no new arrhythmias or ECG changes within this timeframe, and no further elevation in myocardial injury marker levels

Patients capable of using a smartphone

Patients who understood the purpose of this study and voluntarily provided written informed consent

---

Exclusion criteria

---

Previous PCI surgery

Out of age

Patients with significant postoperative wound bleeding, severe infection, fever, severe electrolyte–acid–base imbalance, severe hypoxia, or malnutrition

Patients classified as having cardiac function grades 4

Patients with hepatic and renal failure

Patients with severe physical mobility impairments

Refusal to sign consent form

Mental abnormality

Not suitable for participation

---

***Early termination of the study***

This study may be temporarily suspended or terminated early if there is good and reasonable cause for such termination.

|                                                                                |
|--------------------------------------------------------------------------------|
| Suspended or terminated criteria                                        |
| Determination of unexpected, significant or unacceptable risks to participants |

|                                                                         |
|-------------------------------------------------------------------------|
| Identify patients who may be at risk for an Serious Adverse Events(SAE) |
| Inadequate compliance with protocol requirements by the investigator    |

## Interim analyses

No interim analyses were planned or conducted.

## Screening, Randomization, and Follow-up Flowchart

[figure not shown]

## Study Procedures

### Intervention Strategy

According to the UA treatment guidelines, standardized treatment is provided to all patients, alongside essential knowledge regarding UA and PCI. In the multidimensional digital cardiac rehabilitation intervention group, patients received rehabilitation therapy managed by a multidisciplinary intervention team led by nurses. In this intervention teams, the Cardiovascular Medicine Nurse Manager was the primary person responsible for management of the project. One nursing evidence-based specialist screened expert panellists; four cardiovascular clinicians

and two rehabilitation physicians were involved in the design and implementation of the program; and 2 postgraduate students, consisting of stakeholders on a multidisciplinary team, were involved in the collection of statistical data and analysis of the data.

The multidimensional digital cardiac rehabilitation intervention was delivered through a customized digital cardiac rehabilitation program. The program includes seven key dimensions of rehabilitation: exercise, medication management, nutritional guidance, psychological support, sleep management, health education, and smoking cessation assistance.

### ***1. In-hospital phase***

The primary objective was to prepare patients for long-term recovery by providing education, personalized intervention, and comprehensive support.

#### ***1.1 Exercise Training***

Exercise rehabilitation is a critical component of recovery following PCI, and the intervention group received personalized exercise plans designed to enhance cardiovascular health and physical capacity. During hospitalization, nurses delivered the exercise programs using multimedia-equipped bedside tablet computers, incorporating a variety of interactive materials such as instructional videos, images, and written explanations to ensure patients performed exercises correctly. Nurses provided one-on-one guidance during twice-weekly sessions, with a particular focus on progressive muscle strengthening, aerobic training, and flexibility. To accommodate varying physical capabilities, the exercise program was developed using Flash frame-by-frame animation technology, which allowed for clear visualization of movements, making it easier for patients to follow and execute exercises accurately.

Unlike previous studies, this research tailored the exercise interventions specifically for UA patients undergoing PCI, ensuring the exercises were suitable for individual fitness levels. The program incorporated "Baduanjin" exercises, optimizing movements based on patient age and physical condition, and ensuring accessibility for a diverse range of patients. Each participant received a written rehabilitation

prescription, which included a warm-up phase, aerobic training, strength training, balance exercises, and a cool-down period. The intensity of exercises was adjusted based on the patient's Borg score following a 6-minute walking test, combined with noninvasive cardiac output monitoring to ensure safety and effectiveness.

This individualized rehabilitation program was integrated into the bedside tablet computers, allowing patients to learn and replicate exercises through interactive content. Nurses reinforced the proper execution of the program, ensuring that the rehabilitation process was followed correctly and effectively. The overall goal was to provide a comprehensive, personalized exercise regimen that supported recovery, enhanced physical capacity, and catered to the diverse needs of the patient population.

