## **Study Purpose**

**Primary Objective:** To assess improvement in 6-minute walk test (6MWT), 12-item Short Form Health Survey (SF-12) scores, and frailty phenotypic scores in UA patients undergoing PCI at 3 months postoperatively.

**Secondary Objectives:** To evaluate the changes in gait speed, 30-second chair stand test (30-s CST), grip strength, waist circumference (WC), body mass index (BMI), total cholesterol (TC), high-density lipoprotein cholesterol (HDL-C) levels, low-density lipoprotein cholesterol (LDL-C) levels, and triglycerides (TG) levels were assessed three months after PCI in patients with UA.

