### **Control group**

The control group received only routine nursing care and health education, which was implemented through verbal education combined with the "317 Nursing Education Platform"; routine health education included admission education, preoperative and postoperative education, discharge guidance, and health education at any time during the treatment process. In the control group, no specific individual exercise instructions were provided, especially regarding preoperative and postoperative activities.

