### **Study Outcome**

All clinical outcome measurements were obtained at the three-month follow-up. The primary outcomes included differences in the 6MWT, the SF-12 scores, and the frailty phenotype scores. Secondary outcomes comprised step speed, 30s-CST, grip strength, WC, BMI and changes in lipid profiles (TC, HDL-C, LDL-C, and TG) at 3 months.

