### ***Physical Fitness***

The assessment of physical fitness parameters, including grip strength, walking speed, and balance, was conducted at two time points: upon admission and at the three-month follow-up. ① Grip strength was measured via an electronic grip device (manufacturer model: Guangdong Zhongshan Xiangshan Scale Instrument Co., Ltd. EH201R). During the measurement, a sitting position was maintained, the upper limbs naturally drooped at the side of the body, the palm faced the body, the grip metre handle faced outwards, the grip posture was adjusted according to palm size of the palm, and the grip metre was forced for measurement. A stable attitude was maintained during the measurement, and the grip metre was not swung back and forth. The grip strength of the dominant hand was measured 3 times, and the maximum value was taken as the final measurement result. ② Step speed: 4.6 m. The investigator used a stopwatch (model: new Dragon XL-011) to measure step speed in "s" (to 2 decimal places). ③ 30-s chair standing test: A straight back chair (sitting height of 43.2 cm) was used, and the patient was informed of the evaluation process and shown the movement before the test. The seat was placed against the wall, and the patient sat in a chair with their back straight, feet flat on the ground, and arms and

wrists crossed and held at the chest. When the test began, the patient completed 1-2 exercises, performed the preexperiment, and then started the timed test. The correct movement was as follows: completing the full standing position and then sitting down. If the patient's buttocks could touch the chair seat position, the above movements were repeated as much as possible within 30 s, and the effective number of movements was recorded. ④ BMI was calculated as follows:  $BMI = \text{body weight kg}/(\text{height m})^2$ ; and waist circumference per cm was measured.

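### The plan specifies no baseline 6MWT for controls, so the stated improvement cannot be derived, and an unadjusted 3-month difference has other possible explanations

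*Combined protocol and SAP*

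**What the plan says.** All references are to the combined protocol and SAP.

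- **Objective (Study Purpose).** The primary objective reads "To assess improvement in 6-minute walk test (6MWT), 12-item Short Form Health Survey (SF-12) scores, and frailty phenotypic scores" at 3 months after the procedure.
- **Outcome (Study Outcome).** "The primary outcomes included differences in the 6MWT, the SF-12 scores, and the frailty phenotype scores". On timing: "All clinical outcome measurements were obtained at the three-month follow-up".
- **Early 6MWT (1.1 Exercise Training, in-hospital phase).** "The intensity of exercises was adjusted based on the patient's Borg score following a 6-minute walking test". The section concerns one arm: "the intervention group received personalized exercise plans designed to enhance cardiovascular health and physical capacity".
- **Controls (Control group).** "In the control group, no specific individual exercise instructions were provided". The section describes nursing care and education and does not mention the 6MWT.
- **Admission measurements (Physical Fitness; Blood lipid indices).** "The assessment of physical fitness parameters, including grip strength, walking speed, and balance, was conducted at two time points", namely admission and 3 months. Lipids are also taken at admission. Neither section names the 6MWT.
- **Test method (6-Minute Walking Test).** This section describes how the walk is done. It gives no visit, no practice walk and no handling of repeat tests.
- **Analysis (Statistical Method).** Groups are compared by t test or Wilcoxon test. There is no change score, baseline covariate or repeated-measures model.
- **Comparability (Study Design; Randomization).** Arms were formed by admission date, then matched 1:1 on a propensity score, leaving 68 per arm. The covariates named do not include the 6MWT.

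**The concern.** Improvement needs a starting value, and a comparison of improvement needs one in both arms. The plan specifies none for controls. In the intervention arm, the early walk serves to set exercise intensity. Its timing relative to PCI and to the first programme session is not fixed, so it is not a defined baseline either.

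That leaves a 3-month contrast between non-randomised arms. Randomisation would have made prior walking capacity comparable in expectation. Here that rests on matching, and the matching list does not name the 6MWT. In addition, if the plan was followed literally, intervention patients had walked the test before the outcome visit and controls had not. Walking distance depends on effort and may depend on familiarity with the test.

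A 3-month difference could then come from rehabilitation, prior capacity or unequal testing, and the specified data cannot separate these. The stake is the claim itself: the Discussion already concludes that the programme improved the 6MWT relative to standard management.

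**Working it through.** **Step 1: the schedule, by arm.** The plan states no sample size calculation, effect size or SD for the 6MWT, so there is no figure of its own to reproduce. The main check is of the text.

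| Item | Intervention | Control | Section |
|---|---|---|---|
| 6MWT in hospital | Specified, to set exercise intensity; day and number of walks not given | Not mentioned | 1.1 Exercise Training; Control group |
| 6MWT at admission as an assessment | Not named | Not named | Physical Fitness; 6-Minute Walking Test |
| 6MWT at 3 months | Specified | Specified | Study Outcome |
| 6MWT among matching covariates | Not named | Not named | Randomization |
| Baseline adjustment | None | None | Statistical Method |

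The change in 6MWT is the 3-month value minus the baseline value. The second term is unspecified for controls, so the between-arm comparison of change cannot be formed from the specified data. SF-12 and the frailty phenotype likewise have no stated baseline visit.

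**Step 2: how far a non-treatment shift could matter.** This is a sensitivity calculation. Inputs: n = 68 per arm (Randomization); alpha 0.05 (Statistical Method), with two-sided testing assumed because the plan does not state it. Assumed: no true treatment effect, and a shift *b* (in SD units) in the intervention arm's 3-month mean, whether from familiarity or from carried-over walking capacity.

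- SE of the difference = √(2/68) = 0.171 SD.
- Rejection probability = 1 − Φ(1.960 − b/SE) + Φ(−1.960 − b/SE).
- Example, b = 0.10: b/SE = 0.583, giving 0.0843 + 0.0055 = 0.0898.

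| Assumed b (SD) | b/SE | False-positive rate |
|---|---|---|
| 0 | 0 | 5.0% |
| 0.05 | 0.292 | 6.0% |
| 0.10 | 0.583 | 9.0% |
| 0.20 | 1.166 | 21% |
| 0.30 | 1.749 | 42% |

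In metres, an assumed retained repeat-test gain of 0% to 5% on an assumed 400 m walk is 0 to 20 m (0.05 × 400 = 20). The range includes zero. It cannot be converted to SD units, because the documents give no SD.

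**Step 3: what a common baseline would add in precision.** The difference detectable with 80% power from 3-month values alone is (1.960 + 0.842) × 0.171 = 0.48 SD. Adjusting for baseline multiplies this by √(1 − r²), where r is the assumed correlation between baseline and 3-month values.

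| Assumed r | Detectable difference (SD) |
|---|---|
| 0.3 | 0.46 |
| 0.5 | 0.42 |
| 0.7 | 0.34 |

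**The case against.** The strongest reply is that the text is incomplete rather than wrong.

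- The timing sentence in Study Outcome does not say that outcomes were measured only at 3 months. Grip strength, walking speed and lipids are outcomes in the same section, and other sections give them admission values.
- The Control group section describes care, not assessments. The assessment sections carry no restriction by arm, and the list under Physical Fitness is open-ended.
- The Discussion reports time effects for quality of life, although SF-12 has no stated baseline visit. Some unlisted baselines were therefore probably taken. It lists no time effect for the 6MWT.

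All of this stands, and it rules out stronger readings. A reader might infer that controls walked the test for the first time at 3 months and that the result is biased towards the intervention. The documents do not establish either. A reader might also picture the early walk as coached, but section 1.1 describes guidance for the exercise sessions and says nothing about how that walk was run. Nor should 0 to 20 m be set against the 15%-20% gain in the Introduction. That figure is background from initial studies, not this trial's expected effect.

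The reply does not remove the gap. The baseline of a primary outcome should not have to be inferred. Even if control baselines exist, the planned tests do not use them.

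**Conclusion.** The point holds as a statement about the plan as specified. A 6MWT before 3 months appears only in the intervention arm's exercise prescription, none is specified at baseline for controls, and the comparison is unadjusted between arms allocated by date and matched without naming the 6MWT. Improvement is therefore not derivable from the specified schedule, and a 3-month difference may partly reflect prior walking capacity or unequal prior testing.

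The size of any bias is unknown and may be zero. The false-positive rates of 9% to 21% rest on assumed shifts of 0.10 to 0.20 SD, two-sided testing and a normal approximation; the 0 to 20 m range is likewise assumed. The correction should be made because it concerns a primary outcome in a non-randomised comparison and is cheap. It does not show that the reported finding is false.

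**What to change.** 1. List 6MWT, SF-12 and the frailty phenotype as baseline measurements in both arms, with the same instructions, at the same point relative to PCI and before the first programme session. If control baselines were already collected, document them and use them.
2. Define the primary contrast as the 3-month value adjusted for its baseline. Adjustment addresses measured prior capacity. It does not remove an effect of extra walks in one arm, so also state how many 6MWTs each arm performed and when.
3. If controls have no baseline 6MWT, report a 3-month group difference rather than improvement, align Study Purpose and the Discussion with that, and disclose unequal prior testing as a possible bias.

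**Cost.** With data collection closed, the cost is clarification plus one reanalysis, or a weaker claim if no control baselines exist. In any future use of the plan, it is one short walk per control patient.
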